## Abstract

**Introduction:**

Obstructive sleep apnoea (OSA) is a common, but underdiagnosed, sleep disorder. If
untreated, it leads to poor health outcomes, including Alzheimer’s disease,
cancer, cardiovascular disease and all-cause mortality. Our aim is to determine the
feasibility and cost-effectiveness of moving the testing for OSA into general practice
and how general practitioner (GP)-based screening affects overall detection rates.

**Methods and analysis:**

Randomised controlled trial of case finding of OSA in general practice using a novel
Medicines and Healthcare products Regulatory Agency-registered device (AcuPebble SA100)
compared with usual care with internal feasibility phase. A diverse sample of general
practices (approximately 40) from across the West Midlands Clinical Research Network
will identify participants from their records. Eligible participants will be aged
50–70 years with body mass index >30 kg/m^2^ and diabetes
(type 1 or 2) and/or hypertension (office blood pressure >145/90 mm Hg or on
treatment). They will exclude individuals with known OSA or chronic obstructive
pulmonary disease, or those they deem unable to take part. After eligibility screening,
consent and baseline assessment, participants will be randomised to either the
intervention or control group. Participants in the intervention arm will receive by post
the AcuPebble sleep test kit. Those in the control arm will continue with usual care.
Follow-up questionnaires will be completed at 6 months. The study is powered (90%) to
detect a 5% difference and will require 606 patients in each arm (713 will be recruited
to each arm to allow for attrition). Due to the nature of the intervention, participants
and GPs will not be blinded to the allocation.

**Outcomes:**

Primary: Detection rate of moderate-to-severe OSA in the intervention group versus
control group. Secondary: Time to diagnosis and time to treatment for intervention
versus control group for mild, moderate and severe OSA; cost-effectiveness analysis
comparing the different testing pathways.

**Ethics and dissemination:**

The trial started on 1 November 2022. Ethical approval was granted from the South
Central Oxford A Research Ethics Committee on 9 June 2023 (23/SC/0188) (protocol
amendment version 1.3; update with amendment and approval to renumber to V2.0 on 29
August 2023). Patient recruitment began on 7 January 2024; initial planned end date will
be on 31 April 2025.

Results will be uploaded to the ISRCTN register within 12 months of the end of the
trial date, presented at conferences, submitted to peer-reviewed journals and
distributed via our patient and public involvement networks.

The University of Warwick will act as the trial sponsor. The trial will be conducted in
accordance with the Sponsor and Primary Care Clinical Trials Unit standard operating
procedures.

**Trial registration number:**

ISRCTN 16982033.

STRENGTHS AND LIMITATIONS OF THIS STUDYThis study uses a randomised controlled trial protocol which is written in accordance
with the Standard Protocol Items: Recommendations for Interventional Trials.The study will examine multiple outcomes, including effectiveness of case finding for
obstructive sleep apnoea (OSA) in general practice, time to diagnosis in both arms and
associated full health economic analysis.The study uses a novel OSA testing device which is automatic and intended to speed up
testing and analysis time.The study is limited in that only those individuals currently defined as being at high
risk of OSA (obese with hypertension and/or diabetes) are eligible to take part.Due to the nature of the study, general practitioners and patients cannot be blinded to
the randomisation.

## Introduction

### The problem

 Obstructive sleep apnoea (OSA), often referred to as obstructive sleep apnoea/hypopnoea,
is a common sleep disorder, which if untreated leads to poor health outcomes, including
Alzheimer’s disease, cancer, cardiovascular disease (CVD) and all-cause
mortality.^1^,^3^
Although in the UK it is estimated that 1.5 million adults are living with OSA, up to 85%
of cases remain undiagnosed.^4^
Characterised by repetitive partial or complete blockages of the airway during sleep, it
leads to interruptions in breathing, raised heart rate, raised blood pressure (BP), blood
oxygen desaturation and arousals. In about 60% of patients, OSA is associated with
excessive daytime sleepiness (EDS) and is known as obstructive sleep apnoea syndrome
(OSAS).^5^ OSAS has a negative impact on
quality of life and increases the risk of road traffic accidents (RTAs) by 1.3–7
times.^6^

Recent National Institute for Health and Care Excellence (NICE) guidelines recognise the
need for improved recognition, diagnostic testing and treatment for this condition, with
testing being offered to all people with suspected OSA.^7^ However, there is no systematic approach to identifying patients
with OSA in the general population. Not all patients with OSA experience characteristic
symptoms, including poor sleep quality, snoring, impaired alertness, cognitive impairment,
nocturia, morning headaches, sexual dysfunction and EDS.^8^ Many rely on their partner’s observations of breathing
during sleep, and 42% of people who snore or whose partner snores have not heard of OSA
and would not discuss these symptoms with their general practitioner (GP).^4^ In the UK, suspected cases are currently
diagnosed with sleep studies through specialist hospital referrals but there is a mismatch
between healthcare requirements and sleep service delivery.^9^ For example, at the University Hospital Coventry and Warwickshire
National Health Service (NHS) Trust, prior to the pandemic, the time to treatment was much
longer than 4 months. Nationally, the backlog of patients awaiting a sleep study was
exacerbated during the pandemic, with many sleep service clinical leads being redeployed
to COVID-19 duties and sleep testing protocols redesigned.^10 11^

This study aims to address the need for high-throughput COVID safe testing by evaluating
the feasibility and effectiveness of a novel OSA diagnostic device in a general practice
setting with individuals who are at high risk for OSA.

### Why is this research important?

Treatment of moderate-to-severe OSA with continuous positive airway pressure (CPAP)
improves the health and well-being of patients and the management and control in those
with moderate-to-severe hypertension. It reduces CVD risk markers^12^ and associated adverse CVD outcomes.^13^ CVD accounts for 42% of deaths in people with untreated
OSA compared with 26% of people without it.^14^ Healthcare costs associated with CVD are high and could be reduced
by increased detection and treatment of moderate-to-severe OSA.^4 15^ EDS accounts for ~20% of all RTAs; many of these
involve drivers with undiagnosed OSAS and hence might be preventable. In a national
survey, at the time of OSA diagnosis, 22% had been doing a job requiring them to drive
regularly (27% professionally) and 11% had fallen asleep driving.^4^ As well as personal costs, each fatal accident costs
society around £1.5 million.^4^

### Review of the evidence

In OSA, complete closure (obstruction) of the airway during sleep stops airflow (apnoea),
whereas partial obstruction decreases airflow (hypopnoea) resulting in episodes of brief
awakening from sleep (arousals) to restore normal breathing.^16^ The number of apnoeas/hypopnoeas per hour of sleep
defines the apnoea-hypopnoea index (AHI) and gives an indication of disease severity.^17^ In 1993, the prevalence of OSA was 4% in
middle-aged men and 2% in middle-aged women (ages 30–60 years).^14^ In 2019, Benjafield *et
al* estimated that 425 million adults aged 30–69 have moderate-to-severe
sleep apnoea globally.^18^ In a study
published in 2021, using the Clinical Practice Research Datalink, which represents 8.5% of
primary care practices in the UK, the prevalence of OSA in obese patients was 8.4% in men
and 3.7% in women.^19^ Male sex, high body
mass index (BMI), hypertension and diabetes were the most common risk factors.^19^ The new NICE guidance recognises that OSA
is also highly prevalent in individuals with other conditions like polycystic ovary
syndrome, atrial fibrillation and hypothyroidism.^7^ Higher prevalence rates have been reported in some high-income
countries.^20 21^ OSA is associated
with both type 1 and type 2 diabetes^19 22 23^ and increased BMI,^19 24^ and is a frequent cause of resistant hypertension.^25^,^27^

Current NICE guidelines recommend that adults who are sleepy while driving or working
with machinery, are employed in hazardous occupations (eg, pilot, bus or lorry driver) or
show signs of respiratory or heart failure (with symptoms suggestive of OSA) should be
referred urgently to sleep centres.^28^
However, GPs may not always ask sleep-related questions, and information received may not
be followed up or acted on.^29^ Indeed,
20% of people with OSA had visited their GP on three or more occasions with symptoms and
no action was taken in 11%.^4^

The most common form of treatment is CPAP,^2^ although other treatments are used.^30^ Treating moderate-to-severe OSA can generate health benefits and
improve the quality of life of patients, especially those with OSAS who experience an
improvement in EDS, and a reduction in risk of RTAs.^31 32^ CPAP is also an effective management in patients with
resistant hypertension.^4^

In 2008, NICE appraised the use of CPAP compared with lifestyle management and dental
devices for the treatment of adults with moderate-to-severe OSA. It concluded that CPAP is
cost-effective with a cost per quality-adjusted life-year (QALY) gained below
£5000.^3^ Following a more recent
evidence review, NICE guidelines (2021) currently suggest that people with mild OSAS (ie,
those with EDS) should also be offered treatment using a fixed-level CPAP.^7^ It also recommends that people’s
sleep history should be assessed in individuals with two or more of nine listed common
features of OSA which include snoring, witnessed apnoeas and unrefreshing sleep.^7^

Few studies have attempted a targeted case finding approach for OSA in primary care. In
Canada, researchers asked family doctors to identify patients at high risk (BMI≥30,
type 2 diabetes, treated hypertension or ischaemic heart disease). The prevalence of
undetected OSA was high (71% had mild OSA defined as AHI ≥5 to
<15/hour; 33% had moderate AHI defined as ≥15 to <30/hour; 16%
had severe AHI defined as ≥30/hour).^33^ However, a suggestion that OSA screening could move into general
practice has not been formally tested or evaluated in the UK.^34 35^

Current practice varies across the UK with complex referral pathways; some sleep services
offer a simple overnight oxygen test (oximetry) as a first-line test; others offer home
respiratory polygraphy (RP). Polysomnography is rarely used, requiring overnight admission
to a secondary care sleep facility. For example, in Coventry and Warwickshire, patients
referred by GPs are currently required to visit a hospital to be trained how to use the
sleep study device (eg, NOX T3 (ResMed)). This takes the form of a 30 min
appointment with further written and online instructions for patients to follow. Having
slept overnight with the device’s set of wired sensors at home, the patient brings
the equipment back to the sleep centre for the data recorded to be uploaded and analysed.
The multiple arrays of equipment must then be decontaminated with respect to COVID-19
procedures. Around 15–20% of sleep tests need repeating due to incorrect sensor
placement.^36^ A sleep/respiratory
specialist spends about 2 hours manually scoring each test for diagnosis.

Implementation of the latest NICE recommendations in England will substantially raise the
number of people being referred to sleep services. There is, therefore, an even greater
and more urgent need for a new, rapid and cost-effective way to diagnose
moderate-to-severe OSA, to produce health gains from the use of effective treatments and
to tackle the increasing waiting lists for diagnosis.

### A new medical device

The Medicines and Healthcare products Regulatory Agency (MHRA)-registered AcuPebble SA100
(referred to as AcuPebble) from Acurable provides a simple and potentially cost-effective
option. Its patented technology derives from over 10 years of research at Imperial College
London^37^ (see figure 1).

**Figure 1 F1:**
[figure not shown]
AcuPebble SA100 device (scale in centimetre). Image created by [name].

It is clinically validated and has been found to be acceptable to patients.^38^ It is equivalent to current ambulatory
gold standard (multichannel RP with manual specialist interpretation) based on recommended
American Academy of Sleep Medicine AHI criteria with a positive predictive value of 94.4%
and a negative predictive value of 95.83%.^36^ The system is easy to use; 100% of 150 patients recruited for the
clinical validation were able to follow the simple accompanying instructions.^38^ The AcuPebble is equivalent to home RP,
the NICE-recommended test, with the additional benefits to the patient that it can be
deployed in a faster and COVID-secure way. No hospital attendance is required, it is
posted to patients and its use does not require training, saving patients’ time and
travel costs. The test is comfortable, non-invasive, using a small device attached to the
neck over the throat and so allows more natural sleep, without being attached to leads or
wires.

There are benefits for healthcare providers and the NHS. Staff no longer need to prepare
equipment, train patients or manually interpret recorded signals. The AcuPebble SA100
employs fully automated diagnosis, and its ease of use can release over 1500 hours
annually of clinical staff time (based on an average unit seeing 1000 patients annually)
(Acurable in-house data). The number of tests that need repeating is significantly lower
(less than 1%) than the current approaches to home testing, so helping to cut the
excessive waiting times to achieve the recommended 4-week referral-to-treatment NHS
target.^39^

## The Trial

This protocol is written in accordance with the Standard Protocol Items: Recommendations
for Interventional Trials. Any amendments to the protocol will be reported in the study
article.

Please see online supplemental appendix 1 for a full list of abbreviations used in this protocol.

### Aims and objectives

The aim of this randomised controlled trial is to test the feasibility of moving the
testing for OSA into a general practice setting using the AcuPebble device and to trial a
targeted moderate-to-severe OSA case finding programme. Our objectives are (1) to
determine if using this device would increase the detection of moderate-to-severe OSA in
high-risk groups within general practice, (2) to assess the cost-effectiveness of
screening for moderate-to-severe OSA with AcuPebble in primary care versus usual care in
people at high risk and (3) to compare a new general practice-based route for the
diagnosis of moderate-to-severe OSA with the standard hospital-based referral pathway.

## Methods and analysis

### Trial design

We are conducting a multicentre, pragmatic, individually randomised, parallel-group,
superiority trial and economic evaluation to determine the effectiveness and
cost-effectiveness of using a novel MHRA-registered device (AcuPebble SA100) to detect
moderate-to-severe OSA in a high-risk group compared with usual care.

The study includes a 2-month internal feasibility phase, in which ‘Stop-Go’
criteria will be used to evaluate the implementation of AcuPebble SA100, recruitment and
adherence to the intervention.

### Study setting and recruitment

Participants will be recruited from participating UK general practices in the West
Midlands Clinical Research Network (CRN) region (Warwickshire, West Midlands,
Worcestershire, Herefordshire, Shropshire and Staffordshire). General practices will be
recruited to include different practice types according to list size (small
<6000 to large >12 000 patients), deprivation index,
rural/urban location and practice type (group practice, etc). Participating general
practices, supported by the local CRN and research team, will search their records to
identify and invite eligible patients meeting the inclusion criteria.

### Eligibility

#### Inclusion criteria

Adults aged between 50 and 70 years with BMI≥30 kg/m^2^ as of GP
records in the last 3 years AND documented (a) diabetes (type 1 or 2) OR (b)
hypertension (office BP>145/90 mm Hg or on treatment) OR (c) both (hypertension
and diabetes).

#### Exclusion criteria

Patients with known OSA, with known moderate-to-severe chronic obstructive pulmonary
disease and those deemed unable to take part by their GP (eg, terminally ill, unable to
give consent, etc). Patients with known allergy to acrylate.

### Intervention arm

Participants randomised to the intervention arm will receive the overnight sleep testing
AcuPebble device from Acurable by post. Simple participant instructions, including how and
where the device is placed, are given via a dedicated mobile app (phone supplied with app
if required). Should the test fail, a new test code will be sent to the participant
enabling a repeat test before the device is returned in prepaid addressed envelope. When
the test is complete, the test data are automatically uploaded directly to
Acurable’s secure platform, allowing them to provide the diagnosis, as validated in
their study, using their algorithm.

The sleep study platform will include the Epworth Sleepiness Scale (ESS) and an optional
brief questionnaire to assess acceptability of the intervention. The number of
completed/valid tests, number of failed tests and returned devices will be an indication
of feasibility. Participants are expected to perform the sleep testing within a week of
receipt of the AcuPebble device. Participants will be followed up remotely 6 months from
the date of randomisation. Data will be collected both from participants and medical notes
review.

The results of the sleep studies will be reviewed by our sleep consultant to confirm any
diagnoses of OSA. He will notify the participant’s GP of the results and advise
whether the patient needs to be referred to the sleep clinic for treatment or further
investigation.

### Control arm

Participants randomised to the control arm will continue with usual care provided by
their GP. Patients presenting to the GP with symptoms of OSA will be referred for
assessment through their local usual care pathway as per the NICE guidelines. Participants
will be followed up remotely 6 months from the date of randomisation. Outcome data will be
collected both from participants and medical notes review.

### Trial procedures

#### Informed consent

Written informed consent (see online supplemental appendix 2) will be obtained by appropriately trained members of
the research team. Potential participants are contacted via post; if they express
interest, the research team will explain the study and answer any questions; and if they
are willing to continue, they are asked to complete a consent form. The original signed
copy will be kept in a locked filing cabinet in the dedicated locked trial office.

##### Baseline assessments

Following informed consent and *before* randomisation, participants
will be asked to complete the following questionnaires: EuroQol Heath Status
Questionnaire (EQ-5D-5L) with visual analogue scale (VAS)^40^ and Client Service Receipt Inventory (CSRI).

### Randomisation and blinding

Figure 2 shows the design of the study. Participants
will be randomised (1:1) to receive the intervention or usual care using a validated
web-based randomisation programme (sortition). Randomisation will be minimised with a
non-deterministic minimisation algorithm to ensure site, age (<60/≥60
years), sex (F/M) and ethnicity (White/Other) are balanced across the two groups.
Individual randomisation is appropriate because the risk of contamination is very low,
since the device is sent to participants directly and the assessment of the primary
outcome (diagnosis of moderate-to-severe OSA) will be automated (unbiased).

**Figure 2 F2:**
[figure not shown]
Trial flow diagram. BMI, body mass index; BP, blood pressure; CRN, Clinical
Research Network; GP, general practitioner; OSA, obstructive sleep apnoea.

Due to the nature of the intervention, participants and their GPs will not be blinded to
the allocation of intervention. But the primary outcome can be considered blinded as it is
fully automated. The statisticians will remain blinded to the allocation when performing
data analysis.

### Follow-up

Participants will be followed up at 6 months from point of randomisation. All
participants will be asked to complete repeat measures of the EQ-5D-5L with VAS, CSRI and
a short OSA questionnaire. Two reminders will be sent, but any participants who have not
returned their completed questionnaires within 1 month of the date of posting will
be considered non-responders and their questionnaires considered missing.

The GP notes of all participants in the usual care group will be reviewed to identify any
diagnoses of OSA since randomisation (primary outcome) and for those with a positive
diagnosis, time to diagnosis, time to commencement of treatment and type of treatment
prescribed.

For those in the intervention group *diagnosed with OSA* since
randomisation, their GP notes will be reviewed to determine time to commencement of
treatment and type of treatment prescribed. The GP notes of those who were referred for
further investigation will also be reviewed to confirm whether a subsequent diagnosis of
moderate-to-severe OSA was made, and if so, details of any treatment started.

Reviewing the GP notes of those in the intervention group who tested negative for OSA and
needed no further follow-up is considered unnecessary, as no further information is
required for this trial, and hence there is no justification for accessing
participants’ medical information. A variety of means of communication will be used
to both raise awareness in the practice and to gain a response or to send invitations.
Texts and emails will also be used where appropriate.

Any subsequent post-trial visits and treatment by the GP or sleep clinic are not part of
the research and represent a return to the usual care pathway after diagnosis.

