#### Secondary outcomes

Time to completion of testing from randomisation, time to diagnosis from
randomisation and time to treatment from randomisation for new pathway (intervention
group) versus usual care. For those diagnosed with moderate-to-severe OSA (as
detailed above for both the intervention and usual care groups) and OSAS, their
AcuPebble or GP notes will be reviewed 6 months after randomisation to
determine time to completion of testing, time to diagnosis, time to commencement of
treatment and type of treatment prescribed. For the usual care pathway, we will also
look at the individual components of the usual referral pathway, that is, time to
test from referral, time to diagnosis from referral, time to treatment from
referral. Date of referral is defined as date when the patient was referred.Detection of participants diagnosed with any OSA (mild, moderate, severe), defined
as an AHI reading of ≥5 to <15 (mild), ≥15 to
<30 (moderate) or ≥30 (severe) episodes per hour for new
(intervention) versus usual care pathway. This will be determined from the AcuPebble
report for those in the intervention group and the GP notes review for those in the
usual care group.Detection of participants diagnosed with OSAS, defined as those with OSA (mild,
moderate, severe (as above)) and with evidence of EDS (ESS score >11) for new
(intervention) versus usual care pathway. This will be determined from the AcuPebble
report for those in the intervention group and the GP notes review for those in the
usual care group.Health-related quality of life associated with new and current pathways. QALYs will
be calculated based on information collected from participants at baseline and
6 months using the EQ-5D-5L.Cost-effectiveness analysis comparing new and current pathways. All participants
will be sent follow-up questionnaires either by email or post (as detailed above);
these will include the EQ-5D-5L with VAS, CSRI and information about procedures
undertaken to diagnose or treat moderate-to-severe OSA since randomisation. Further
data on health service usage will be obtained from the participant notes review
undertaken at 6-month follow-up. This review will collect data on service usage
related to sleep issues in the 6 months prior to date of randomisation to
provide a baseline value and during the 6 months after randomisation to
provide follow-up data.Feasibility and acceptability of new sleep study testing to be tested against the

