### Sample size determination

The detection rate of new cases of moderate-to-severe OSA using usual care is estimated
at <5% per year. Given the previously observed rates of hypertension (39%), obesity
(34%) and diabetes mellitus (15%) in individuals with OSA, we would expect that the
targeted case finding intervention would yield a detection rate of 10% or more in the
high-risk groups. The study has been powered (90%) at 5% two-sided significance level to
detect a 5% difference in rate of new cases of moderate-to-severe OSA between intervention
and usual care. The study will require 606 participants in each arm. To allow for 15%
attrition and lost to follow-up, it is anticipated that 713 in each arm need to be
recruited.

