## Health economic evaluation

A trial-based economic analysis will be undertaken to assess the cost-effectiveness of the
use of AcuPebble in general practice compared with GP referral to hospital for the diagnosis
of people with moderate-to-severe OSA. Information about resource use will be collected
using resource use questionnaires and notes review, which will include equipment (AcuPebble
and home sleep RP) required, staff required and healthcare resource while participants are
awaiting referral and treatment. Resource use will be valued using national sources.^41^

Additionally, we will conduct a systematic literature review to identify existing economic
evidence regarding OSA diagnosis and in individuals with evidence of EDS/OSAS and treatment.
Insights from this and input from clinical experts will inform the model structure. In the
model, we will include a ‘no screening’ strategy to model the natural history
of people living with OSA, in addition to the two screening approaches: using AcuPebble in
general practice and GP referral to hospital-based standard care (home sleep RP). We
envisage the economic model will comprise two stages. In the first stage, we will use a
decision tree illustrative structure to model the short-term costs and benefits associated
with identifying people living with OSA and in individuals with evidence of EDS/OSAS
following screening. In the second stage, we will use a state transition Markov structure to
model the progression of events associated with moderate-to-severe OSA (eg, stroke, CVD,
myocardial infarction), and RTAs in those with individuals with evidence of EDS/OSAS, then
the long-term costs and benefits associated with treatment following the screening/no
screening strategies.

The economic model will require clinical and cost inputs related to the strategies.
Clinical inputs (eg, time to test, time to diagnosis and time to treat) will be obtained
from the clinical trial and supplemented with information from the literature (eg, rate of
moderate-to-severe people with OSA experiencing a stroke, associated costs and utility
values). The cost associated with using AcuPebble will be obtained from Acurable and costs
for GP referral to hospital-based standard care will encompass all resource use and costs
for GP referral using the home sleep RP. Resource use questionnaire will be developed using
the CSRI to capture healthcare associated with diagnosis and patient management while

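### Usual-care referral intervals are extracted only for participants diagnosed by the 6-month notes review, so referrals still pending drop out instead of being censored and the waits are understated

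*Protocol article*

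**What the plan says.** All places are in the protocol article.

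- **Follow-up.** The notes of every usual-care participant are reviewed at 6 months from randomisation to find "diagnoses of OSA since randomisation (primary outcome) and for those with a positive" diagnosis, time to diagnosis, time to starting treatment and treatment type.
- **Secondary outcomes.** Times to test, diagnosis and treatment are taken at the 6-month review for those diagnosed with moderate-to-severe OSA and OSAS. The same paragraph says that for usual care the team will also "look at the individual components of the usual referral pathway, that is, time to" test, diagnosis and treatment, each counted from referral.
- **Statistical methods.** Time-to-event outcomes go to Cox regression. Only time to starting treatment is expressly limited to diagnosed participants. The one stated censoring rule covers participants who do not start treatment, at last contact.
- **Introduction, The problem.** As an example, at one hospital trust "prior to the pandemic, the time to treatment was much" longer than 4 months. The national backlog of patients awaiting a sleep study is then said to have worsened.
- **Health economic evaluation.** "Clinical inputs (eg, time to test, time to diagnosis and time to treat) will be obtained" from the trial, with literature as a supplement.

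**The concern.** A referral-to-event interval measured only in people whose diagnosis fell inside a fixed window is right-truncated. A referral made in month r after randomisation can contribute only if its wait is at most 6 − r months. Long waits are removed from the sample and are not carried as censored observations. The censoring rule in Statistical methods does not bring them back, because it applies to people already diagnosed.

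Time to treatment has a related fault. Restricting it to diagnosed participants conditions on an event after randomisation, and that event occurs at a different rate and time in each arm. The two diagnosed groups are then no longer a randomised comparison.

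Objective 3 compares the general-practice route with the hospital referral route, and the same times feed the economic model. A usual-care pathway that looks faster than it is would distort both. If pending referrals are not recorded with their dates, no later analysis can recover them.

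**Working it through.** **1. The plan's own figures.** The protocol gives no calculation for the waits, so there is none to reproduce. The sample size was checked to see whether power is involved.

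- For 5% versus 10%, 90% power and 5% two-sided, the two-proportion formula gives 582 per arm without continuity correction and 621 with it. The stated 606 is within 2.5% of the latter and has 91.2% power by the uncorrected formula.
- 606 / 0.85 = 712.9, so 713 is exact.
- The usual-care rate is given "at <5% per year. Given the previously observed rates of hypertension (39%), obesity" and so on, but the outcome is read at 6 months. If half of 5% (2.5%) is detected by then, 606 per arm gives 98.0% power for a 5-point difference and over 99.9% against 10%. Power is not at issue.

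**2. Who contributes a time.**

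| Usual-care participant at 6 months | Times extracted under Follow-up and Secondary outcomes? |
|---|---|
| Referred, diagnosed, treated | Yes |
| Referred, diagnosed, not yet treated | Yes; treatment censored |
| Referred, not yet tested or diagnosed | None described |
| Never referred | No referral interval exists |

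The third row is where the long waits sit.

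**3. Size when all referrals follow randomisation.** Assumptions, none from the documents: referral time r uniform on 0 to 6 months; wait w from referral either exponential or log-normal (log SD 0.5); the wait is seen only if r + w ≤ 6.

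For exponential waits the share seen has a closed form, 1 − (1 − e^(−6λ)) / (6λ), with λ = ln 2 / median. For a median of 4, 6λ = 1.040 and the share is 1 − (1 − 0.354)/1.040 = 0.378. The other figures come from simulation with at least 2,000,000 referrals per case.

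| True median wait | Share seen | Observed median |
|---|---|---|
| 4 months | 38% (exponential), 32% (log-normal) | 1.4, 2.9 months |
| 6 months | 28%, 15% | 1.5, 3.5 months |

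With a fixed 4-month wait, (6 − 4)/6 = one third would be seen.

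**4. Size when earlier referrals are included.** Eligibility excludes known OSA, but not people already referred. Let referrals occur uniformly from 6 months before to 6 months after randomisation, and keep those still waiting at randomisation.

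| True median wait | Share seen | Observed median |
|---|---|---|
| 4 months | 48% (exponential), 55% (log-normal) | 2.8, 3.8 months |
| 6 months | 37%, 41% | 3.3, 5.2 months |

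The observed median is too short in every case, but the gap ranges from large to slight.

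**5. Does censoring repair it?** In the same simulations, Kaplan-Meier with pending referrals censored at the review returns a median of about 4.0 months when the truth is 4, and does so with earlier referrals too if they enter at randomisation (delayed entry). When the true median is 6 and all referrals follow randomisation, the median lies at or beyond the edge of the window and would usually be reported as not reached. The lower quartile is still recovered (2.5 months exponential, 4.3 log-normal).

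**The case against.** Several points on the other side are sound.

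- **Cox regression is planned.** Only time to starting treatment is limited to diagnosed participants. Time to test and time to diagnosis from randomisation can include everyone, with those lacking the event censored at 6 months. A reader might infer that all the time outcomes are truncated. The documents do not support that.
- **Pending referrals count as not detected.** A reader might call this an error in the primary outcome. It follows from the definition, diagnoses found at the 6-month review, and delay is part of what usual care delivers. It is not misclassification.
- **The 4-month figure.** A reader might take it as the protocol's general statement of the usual-care wait. It is time to treatment, at one trust, before the pandemic, given as an example. The documents give no usual-care time to test or diagnosis.
- **Data capture may be wider than described.** Every control's notes are opened, sleep-related service use is collected, questionnaires ask about diagnostic procedures, and the referral sentence is not itself expressly limited to diagnosed participants. This is the best defence. However, that sentence sits in a paragraph whose extraction rule is for those diagnosed, Follow-up says the same, and nothing links the service-use data to the intervals.
- **Consequences are bounded.** Literature supplements the model inputs, and shortened usual-care waits work against the new pathway in a timing comparison. That limits the harm but leaves the estimate biased.

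**Conclusion.** The point holds for the usual-care intervals from referral to test, diagnosis and treatment, and for time to treatment as restricted to diagnosed participants. As written, the first are right-truncated and the second is conditioned on an event after randomisation. This is a stated extraction rule, not a detail left to an analysis plan.

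The direction does not depend on the wait distribution; the size does. For an assumed true median of 4 months, the observed median is about 1.4 to 2.9 months with all referrals after randomisation, or 2.8 to 3.8 months with earlier referrals included at the same rate. These are illustrations and not estimates for this trial.

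Time to test and time to diagnosis from randomisation are unaffected, provided that the Cox model includes all randomised participants and censors those without the event at the 6-month review. The primary endpoint and its power stand.

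**What to change.** 1. At the usual-care notes review already planned, record every OSA referral with its date and its 6-month status: tested, diagnosed, treated or pending.
2. Estimate the referral-based intervals by Kaplan-Meier in all referred controls. Censor pending referrals at the review date, and use delayed entry for any referral made before randomisation.
3. State that time to test and time to diagnosis from randomisation use all randomised participants, with censoring at the 6-month review.
4. Analyse time to treatment from randomisation in all randomised participants, or label the analysis restricted to diagnosed participants as descriptive. If all are used, state how intervention participants whose notes are not reviewed (those who tested negative) are handled, for example as untreated at 6 months.
5. Keep the 6-month primary endpoint and report the number of pending usual-care referrals beside it.
6. Feed the economic model from the censored estimates.

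The cost is one or two fields on a review done for every control, plus analysis wording. No longer follow-up is needed. The downsides are a slightly longer notes review and wide intervals, because few controls may be referred.
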